### Intervention arm

The patients in the intervention arm will be exposed to the same procedures as those from the active control arm. In addition, they will also receive the mHealth intervention incorporating JITAI principles (Table 2). During the first six months, the mHealth intervention will be supported with human phone counselling (lead-in phase). Then, for the next six months, the mHealth intervention will be fully automated, without any human support (maintenance phase) (Fig. 1).

#### mHealth intervention

The mHealth intervention has been developed with the involvement of (pre)diabetes patients according to the mHealth development and evaluation framework [70, 71]. This framework consists of four sequential phases: (a) conceptualisation, (b) formative research based on focus groups with the target population, (c) pre-testing of specific messages, and (d) piloting [71]. The intervention development and the messages' content and triggering rules will be described in a separate paper. In brief, the patients receive six types of text messages involving various behaviour change techniques (Table 2) [72]. (1) Just-in-time prompts to increase walking pace are triggered when the patient is actually walking (5 consecutive minutes with steps per minute in the range from 60 to 100). (2) Just-in-time prompts to interrupt sitting are sent when the patient sits for more than 30 min. (3) Interim reviews of patients’ weekly step goals are triggered on Friday evening, highlighting the potential discrepancy between the goal and actual step count so that the patients have a chance to catch up over the weekend. (4) At the end of the week, on Sunday evening, patients receive feedback on their weekly performance and encouragement for the upcoming week. (5) Reminders of the action plans are adapted to specific plans of each patient as set during the phone counselling session (e.g., patients are reminded to go for a short walk after lunch or to walk their dog on a pre-specified day and time). (6) Finally, short educational messages are sent occasionally to highlight the importance of PA in (pre)diabetes management.

The mHealth intervention is enabled by the HealthReact system developed at the University of Hradec Kralove [73]. HealthReact consists of a server-side application connected to the Fitbit server and thus can trigger sending out just-in-time text messages based on the data recorded by the Fitbit tracker (Fig. 2). Researchers can choose from a wide variety of just-in-time triggers to suit study objectives and adapt the triggers to the specific needs of individual patients. The HealthReact system enables the setting of certain parameters to regulate the number of text messages sent (e.g., total number of just-in-time prompts per day, the minimum time between two prompts, the time window when prompts are triggered, the probability that a triggered text message is actually sent out). These parameters are tuned so that the total number of text messages per week ranges between 4 and 6.

**Fig. 2 Fig2:**
[figure not shown]
Scheme of the HealthReact system. The HealthReact system triggers sending out just-in-time text messages based on data recorded by the Fitbit tracker

For the mHealth intervention to function optimally, patients must be equipped with a smartphone able to run the Fitbit app (Android 8.0 or iOS 14.0 and later as of January 2023) with a continuous internet connection. Patients who fall short of such requirements will receive adapted mHealth intervention that is equalised for the total number of text messages and the behaviour change techniques used. For example, in patients without a mobile data plan who only sync their mobile when connected to wifi, the prompts to increase their walking pace could not be triggered just in time when they walk, but would still be sent out at a pre-specified fixed time. In patients that do not sync reliably even when at home, the prompts to interrupt sitting could not be triggered just in time and would be replaced with a general reminder to regularly interrupt sitting. Finally, in patients without a smartphone or unable to sync any Fitbit data to HealthReact for other reasons, messages reviewing their step goal and providing feedback could not be personalised, but would still be sent out as simple reminders to review the set goal and provide encouragement.

#### Phone counselling

To facilitate the adoption of the mHealth intervention, counsellors recruited from among the university students and trained by the research team members (CW, TV, JK, JN) will contact the patients by phone at the start of the intervention, at months 1, 2, 3, 4 and 5, and after the six-month assessment (i.e., seven phone calls altogether, each lasting approximately 10 to 20 min). In addition to enabling the implementation and tailoring of the mHealth intervention to individual patients, the counsellors will use various behavioural change techniques (Table 2) to support patients in the desired behavioural change and enhance their adherence to the intervention.

During the first phone call, approximately one to two weeks after the second baseline visit to the GP, the counsellor will check the patients’ baseline mean daily step count as recorded by Fitbit during the previous week when the patients were supposed not to change their physical behaviour. The counsellor will initially recommend the patients increase their daily step count by at least 3000 above their baseline gradually over at least six weeks. However, if patients are not comfortable with the increase of 3000 steps, they can suggest a goal that they feel is more realistic. Importantly, the counsellor will make sure that the patients have a goal that they consider their own and not imposed on them by the counsellor [74, 75]. Finally, the daily step goal will be converted to a weekly step goal (multiplying by 7), allowing more flexibility in planning the walks. Furthermore, the patients will be encouraged to think about the opportunities for taking these extra steps and develop their own action plans. If patients have difficulties devising the action plan, the counsellor can suggest potential opportunities for including walking into their daily routine (walking as part of daily commuting, walking after a meal, walking with (grand)children, walking a dog, walking meetings, etc.).

The information collected during the first call will then be used by the counsellor to set and tailor the mHealth intervention. Specifically, the weekly goal will be used to inform the review of the weekly step goal and feedback on weekly performance, and the action plan will be used to set the content and timing of the respective reminders.

During the next calls (months 1 to 5), the counsellor will support the patients in reviewing their step goals and action plans, address the barriers to achieving their plans, advise them to seek social support, provide them with feedback, and encourage them to increase their walking pace and interrupt their prolonged sitting episodes regularly. During these calls, the counsellor can adjust the mHealth intervention and adapt it to changing patients’ needs. Specifically, if the patients regularly achieve their step goal, the counsellor can challenge them to increase it. The call at five months will be scheduled at least two weeks before the six-month assessment to avoid potential patients’ reactivity that could inflate their PA outcomes at six months.

After the assessment at six months, the counsellor will have a final contact with the patients to encourage them to maintain or further increase their achieved levels of PA and remind them that they will continue receiving text messages for six more months.

### Outcome measures

Outcomes will be assessed at baseline and 3, 6, and 12 months after randomisation, as described in Table 1. The primary outcome is defined a priori as the change in average daily step count from baseline to 12 months. All other outcomes and comparisons are defined as secondary outcomes.

Average daily step count and other measures of physical behaviour and sleep will be objectively assessed by accelerometry using Actigraph wGT3X-BT worn on a non-dominant wrist for seven days, 24 h a day. The measures will be derived from raw-accelerometry files using an open-access package GGIR in R according to standard procedures, including detection of non-wear and calculation of the average magnitude of dynamic acceleration corrected for gravity (Euclidean Norm minus 1 g) over 5-s epochs [76, 77]. Non-wear will be imputed using the default setting, and patients will be excluded if their post-calibration error is > 0.01 g (10 mg) or they have < 3 days of valid wear (defined as > 16 h per day), or their wear data are not present for each 15-min period of the 24 h cycle [78]. The other physical behaviour measures will include average acceleration, intensity gradient, and acceleration above which a person’s most active 10, 30, 120 and 480 min are accumulated, time spent sedentary and in sedentary bouts > 30 min, and time spent in light, moderate and vigorous PA [79, 80]. The sleep measures will be calculated using automated sleep detection [81], without using a sleep log, and will include sleep time (accumulated nocturnal sustained inactivity bouts), sleep window (time difference between falling asleep and waking up, including time being awake during the night), sleep onset and wake time, and sleep efficiency (ratio of sleep time compared with sleep window) [82].

Lower body strength will be assessed by a 30 s chair-stand functional test. The test is administered using a chair without arms, placed against a wall [83]. Fasting plasma glucose, glycated haemoglobin (HbA_1c_), and lipid profile will be assessed by standard laboratory or point-of-care methods available to GPs. The available methods may vary among GPs, but the GPs will be required to use the same method across all assessment points. Blood pressure, height, weight, and waist circumference will be measured to the nearest 1 mmHg, 1 cm, 1 kg, and 1 cm, respectively, using standard calibrated devices available in the GP's office. Symptoms of anxiety and depression will be assessed by the Hospital Anxiety and Depression Scale (HADS), a 14-item questionnaire consisting of depression and anxiety subscales [84]. Health-related quality of life will be assessed by the 12-Item Short Form Health Survey (SF-12) [85].

Patients' sociodemographic characteristics, education level, medical history, current smoking status, alcohol intake, and current medications will be collected (Table 1) and used as confounders in the analyses. In addition, the Morningness-Eveningness Questionnaire (MEQ) for the assessment of patients' chronotype [86] and a short version of the European Health Literacy Survey (HLS-Q12) [87] will be administered at baseline.

In addition to pre-/post-intervention outcomes, the Fitbit data will be used to explore short-term changes in behaviour proximal to the triggered text messages using a micro-randomisation design [88]. Briefly, HealthReact enables setting a probability that a triggered text message is actually sent out, thus enabling micro-randomisation. We will set the probability of sending out each triggered text message to 50% (i.e., only every other text message that is triggered will be actually sent out). Thus, we will be able to compare physical (in)activity, as recorded by Fitbit after the trigger, between text messages that were actually sent and those that were not. For different types of text messages, we will evaluate various time periods after the trigger: for just-in-time prompts to increase walking pace or interrupt sitting, we will evaluate periods ranging from 5 to 15 min; for the action plan reminders, we will evaluate periods ranging from one hour to one day; for the review of the weekly goal and the feedback on weekly performance, we will evaluate periods ranging from one day to one week. In addition, we will explore the moderating effect of the context (e.g., time of the day, day of the week, weather, actual patient performance) on the impact of individual text messages.

#### Adverse events

Adverse events will be monitored and recorded throughout the study period. Data regarding falls, injuries, musculoskeletal problems, hypoglycaemic episodes, major cardiovascular disease events, and any other events potentially related to the study implementation will be collected at all assessments.

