### Sample size

To detect a difference of 1000 steps/day at 12 months between arms, with a power of 80%, using a 2-sided 0.05 significance level (alpha), and anticipating the standard deviation of 3000 steps/day [21, 40, 46], 143 subjects per arm (286 in total) will be needed. To account for an expected attrition rate of approximately 15% [21, 40, 46], we plan to recruit 340 patients for the trial. The increase of 1000 steps/day is equivalent to about 10 min/day of brisk walking [61] and equates to around a 4% decrease in the risk of cardiovascular morbidity and mortality in individuals at high cardiovascular risk with impaired glucose tolerance [62].

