### Patient recruitment and consent

To achieve the target of 340 recruited patients, each of the 21 general practices has been asked to recruit at least 17 patients. To compensate for potential under-recruitment at individual practices, we will allow those practices that reach this target to continue recruiting until 24 patients.

Previous studies of PA interventions in primary care identified a selection bias when GPs preferentially pick those patients whom they believed to be able to use (e.g., highly educated patients) and to benefit from the intervention (e.g., patients with overweight and obesity) [29, 63]. To minimise the selection bias, we first compiled a list of all prediabetes and type 2 diabetes patients for each general practice based on their computerised medical records. At the start of the recruitment, each general practice was provided with a random selection of 24 patients from their list, i.e., 504 patients in total for all 21 practices, stratified by sex (female:male in 1:1 ratio) and condition (prediabetes:diabetes in 1:2 ratio). GPs were instructed to evaluate the eligibility criteria and introduce the study opportunistically to all eligible patients from this selection whenever they appear in the general practice for a routine health check-up [64]. For patients who are excluded or refuse to participate, GPs record the reasons. When a GP expends all the patients from this selection, they will be offered a new random selection of 12 patients from their original list. This procedure can be repeated until the respective practice exhausts its original list or reaches 24 recruited patients.

When introducing the study, GPs will mention that all enrolled patients receive a Fitbit activity tracker that they can retain after completion of the study, irrespective of the trial arm allocation. Those who agree to participate will be asked to sign a written informed consent, including consent for later access to GP records to assess long-term health outcomes. The patients will also consent for the researchers to access their PA data on their Fitbit account in line with the legal requirements.

To minimise the effect of seasonal variability on PA findings, we will attempt to spread patient recruitment evenly across 12 consecutive months. For example, GPs will be only provided with two Actigraph devices necessary for a week-long baseline assessment, so a GP cannot recruit more than four patients per month.

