#### Visits to the GP at 3, 6, and 12 months

During the study period, all patients will visit their GPs for a routine health check-up every three months as recommended by the Czech guidelines for GPs [59, 60]. During visits at 3, 6, and 12 months, they will undergo study assessments (Table 1). Patients who finish the study can retain the Fitbit device.

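### Scheduled adverse event collection leaves a six-month gap across the whole maintenance phase, although an existing nine-month GP visit could halve it

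*Protocol article*

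**What the plan says.** The Adverse events section makes two statements. The first is general: "Adverse events will be monitored and recorded throughout the study period". The second gives the timing for the listed events (falls, injuries, musculoskeletal problems, hypoglycaemic episodes, major cardiovascular events) and closes with "any other events potentially related to the study implementation will be collected at all assessments".

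The assessment times are fixed elsewhere. Outcome measures states: "Outcomes will be assessed at baseline and 3, 6, and 12 months after randomisation, as described in Table 1". The section on GP visits agrees: "During visits at 3, 6, and 12 months, they will undergo study assessments". That same section says that "all patients will visit their GPs for a routine health check-up every three months".

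The Intervention arm section describes the second half of the trial: "for the next six months, the mHealth intervention will be fully automated, without any human support". The Phone counselling section adds that, after the six-month assessment, patients are encouraged to keep up or raise their activity.

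The recruitment section records patients' agreement to the use of their practice records, "including consent for later access to GP records to assess long-term health outcomes".

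**The concern.** The general statement promises continuous monitoring, while the only mechanism described is tied to assessment dates. After month 6 those dates are six months apart, and the routine visit that falls between them is not given a safety role.

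The listed events differ in how easily they come to light. A major cardiovascular event will usually reach the GP. A fall without treatment, a sore knee or a mild hypoglycaemic episode is more likely to go unreported unless the patient is asked, and more likely to be forgotten the longer the interval. Systematic questioning is therefore sparsest during the phase in which the intervention runs without counsellors. That is also the phase which the Discussion proposes could be maintained in the long term. The trial has no independent data monitoring committee, so routine collection is the main source of its safety evidence.

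**Working it through.** The plan states no figure on this point, so the check is of the schedule and of the routes by which events could be recorded.

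**Inputs**
- Assessment months (Outcome measures; Visits to the GP): 0, 3, 6, 12.
- Routine GP visits every three months (Visits to the GP), which implies months 3, 6, 9 and 12 after month 0.
- Maintenance phase (Trial design; Intervention arm): months 6 to 12.

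**Intervals between scheduled collections**
- As written: 3 − 0 = 3, 6 − 3 = 3, 12 − 6 = 6 months.
- Longest interval as a share of follow-up: 6/12 = 50%. It starts and ends with the maintenance phase.
- Collections that close an interval in each phase: two in the lead-in (months 3 and 6), one in maintenance (month 12).
- The only routine visit month that is not an assessment month is 9.

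**With month 9 added**
- 3 − 0 = 3, 6 − 3 = 3, 9 − 6 = 3, 12 − 9 = 3 months.
- The longest interval falls from 6 to 3 months, and each phase has two collections. Sample size and power are unaffected.

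**Other routes by which an event between assessments might be recorded**

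| Contact | Who | Described as adverse event collection? |
|---|---|---|
| Monthly check of Fitbit syncing, with a call to non-syncers | Both arms | No; the stated purpose is a reminder to sync |
| Seven counselling calls, the last after the six-month assessment | Intervention arm only | No; the stated content is goals, plans, barriers and feedback |
| Routine nine-month GP visit | Both arms | Not mentioned |

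None of these is given a safety role in the text. If recording between assessments did depend on counsellor calls, the chance of reporting would differ between arms in the lead-in and would largely disappear afterwards. A form completed by the GP avoids this: GPs see both arms, carry out all assessments and are meant to be blinded to allocation.

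**Size of the loss.** The document gives no event rates and no recall or reporting rates. The number of events missed cannot be calculated from it.

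**The case against.** The strongest reply is that the general statement means what it says. Events are recorded throughout, and collection at assessments is an additional safeguard. The article is a condensed account, the full protocol may set out how recording between visits works, and the schedule in Table 1 is not reproduced in the text available. This stands as far as it goes. A reader might infer that adverse events are collected only at assessments, that the maintenance phase rests on a single six-month recall, or that nothing is recorded at month 9. The document supports none of these. What remains is a stated collection schedule with a long interval and an existing visit to which it assigns no role.

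Four further limits also stand:

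- **Non-attenders.** A reader might infer that events in patients who stop attending are lost, and put the number at 0.15 × 340 = 51. The 15% is an attrition allowance in the step-count sample size. It does not say that these patients have no adverse event records, and they may remain under the care of the same practice.
- **Supervision.** The maintenance phase should not be called unsupervised. The absence of human support refers to the mHealth intervention; routine GP visits and monthly sync checks continue.
- **Comparison between phases.** Unequal intervals could distort a comparison of event rates between lead-in and maintenance, but no such comparison is planned, and the article does not claim safety on that basis.
- **Comparison between arms.** The schedule is the same in both arms, so the six-month gap does not by itself favour either one.

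**Conclusion.** The point holds as an inexpensive improvement to a stated schedule; it does not show that safety data are missing. The scheduled intervals are 3, 3 and 6 months, and the longest covers the entire maintenance phase and half of follow-up. The likely consequence is less complete capture of minor events in that phase, by an amount that cannot be quantified here.

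The conclusion rests on three assumptions: that the nine-month routine visit takes place as the article says, that Table 1 does not already assign adverse event collection to it, and that minor events are reported less completely without systematic questioning. The last is a general judgement and is not taken from the document.

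**What to change.** Complete the same adverse event form at the existing nine-month GP visit, in both arms, so that scheduled collection runs in four equal three-month intervals. State briefly how events that come to light between visits are recorded, so that the general promise has a described method behind it.

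Optionally, check the practice records of patients who miss the 12-month assessment for the listed events. Mark such events by source and report events on all randomised patients. This depends on consent. The stated agreement concerns later record access for long-term health outcomes, and whether it extends to an adverse event check at 12 months must be confirmed first.

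The cost of the main change is one extra form per patient (at most 340), a few minutes of GP time each, and a minor amendment. The record check adds a short review for each patient who misses the final assessment.

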#### Blinding

Due to the nature of the study protocol, the patients and researchers cannot be blinded, as they will both be aware of the allocation due to their active role in the intervention. However, the participating GPs, who will conduct all the assessments, will be blinded to arm allocation unless they specifically ask a patient about their allocation (which the GPs are discouraged from doing). All those conducting the data analysis will also be blinded to group allocation.

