### Data management and analysis

#### Data management

All study data will be collected and managed using secure REDCap electronic data capture tools hosted at Charles University, Prague [69]. To further ensure data confidentiality, data access rights to REDCap will be granted to only a few members of the research team and selectively constrained according to their roles in the trial. Patients' Fitbit data will be stored in a pseudonymised form on a secure HealthReact server. Patients' study information will not be released outside of the study without the patient's written permission.

The trial is not overseen by an independent data monitoring committee as it neither recruits vulnerable populations, poses any unusual risk to trial participants, nor assesses mortality or major morbidity outcomes [89, 90]. The trial results will be disseminated in open-access scientific journals regardless of the magnitude or direction of effect, and a completely deidentified dataset will be made openly available in an appropriate data repository.

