## Discussion

The ENERGISED trial is a pragmatic randomised controlled trial that aims to assess the effectiveness of a mHealth intervention with lead-in phone counselling support that can be potentially translated to routine primary care. The trial has several important strengths.

Firstly, the control arm, against which the intervention will be compared, was designed as an active control. Patients allocated to the active control arm will receive from their GPs brief advice, including a recommendation to self-monitor their daily steps and try to achieve a specific step goal and a Fitbit tracker. The active control was primarily chosen to be able to isolate the net effect of the mHealth intervention. Indeed, given that self-monitoring using a simple activity tracker is effective in increasing PA levels, complex interventions should be compared against a control consisting of self-monitoring and a set goal to demonstrate their additional benefits above and beyond self-monitoring alone [38]. In addition, given the proven benefits of PA for diabetes prevention and management, we consider active control to be a more ethical choice than passive control. Besides, the use of active control has several other advantages: (A) It reflects the growing number of people already using some activity tracker for self-monitoring, thus, enabling their inclusion in the study and, consequently, being more ecologically valid. (B) It increases perceived value for patients even if they are allocated to the control group, thus, increasing the willingness of the patients to be enrolled in the study and limiting the self-selection bias. (C) Along the same lines, it also increases perceived convenience for GPs, making their recruitment for the study easier. (D) As both control and intervention arms receive from their GPs the same treatment, the GPs can be effectively blinded to the patient's allocation. Taken together, the choice of active control increases both the internal and external validity of the trial and is in line with its pragmatic design.

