Finally, the intervention is designed to be scalable so that it can be easily rolled out to routine use in primary care without prohibitive costs and additional burdens on the GPs. The costs include the initial provision of the Fitbit device, but it can be eventually replaced by a cheaper device or a free step-counting app [43]. The costs further include phone counselling during the lead-in phase, which is relatively resource-intensive but necessary to ensure proper implementation and tailoring of the mHealth component. To limit the costs of phone counselling, we recruited counsellors from among the university students and provided them with the necessary training. Following the lead-in phase, the mHealth intervention can be maintained in the long term without substantial costs that only include running a server and sending out text messages (which can be eventually replaced by free app notifications or WhatsApp messages). Importantly, the phone counselling provided by trained counsellors can compensate for the lack of expertise in PA counselling among the GPs. Thus, the intervention does not require either specific training of GPs or their extra time, which are significant barriers to providing PA interventions in primary care [28]. In summary, if shown to be effective, the intervention has the potential to be translated into routine primary care without obstacles on the GPs’ side.

The trial also has several limitations: (1) As GPs in the Czech Republic only follow prediabetes and uncomplicated type 2 diabetes patients not taking insulin, the findings of the trial cannot be generalised to insulin-dependent diabetes patients or those with high HbA_1c_ levels. (2) Despite our effort to keep GPs blinded to patient allocation, we cannot ensure it, as the allocation may become apparent during the discussions with patients at repeated visits. However, this will not impact outcome assessment. (3) The use of innovative technology can be a limitation for some patients who might struggle to set their Fitbits properly. However, this limitation is partly overcome by the provision of phone-based technical support. (4) The intervention only focuses on walking. Even though walking is the most common mode of PA in (pre)diabetes patients and is suitable for nearly everyone [105], it can still be a limitation for some patients who prefer to accumulate their PA by other means (e.g., cycling, swimming).

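### The adverse-event section records events without condition in one sentence and makes suspected relatedness a condition for unlisted events in the next, so non-cardiovascular deaths and other unlisted admissions may go unrecorded

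*Protocol article*

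**What the plan says.** The Adverse events section, under Outcome measures in the protocol article, has two sentences. The first sets a general rule: "Adverse events will be monitored and recorded throughout the study period". It contains no relatedness condition.

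The second says what is gathered at the assessments. It names "falls, injuries, musculoskeletal problems, hypoglycaemic episodes, major cardiovascular disease events" without qualification, then adds a residual category: "any other events potentially related to the study implementation will be collected at all assessments". Deaths from other causes and hospital admissions are not named.

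Three other places bear on the point:

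- The Blinding section says that patients and researchers cannot be blinded, but that "the participating GPs, who will conduct all the assessments, will be blinded to arm allocation unless they specifically ask a patient about their allocation".
- The limitations in the Discussion concede: "Despite our effort to keep GPs blinded to patient allocation, we cannot ensure it".
- The Data management section justifies having no independent monitoring committee partly on the ground that the trial does not recruit vulnerable populations, "nor assesses mortality or major morbidity outcomes".

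**The concern.** In a randomised trial, harms are compared by recording events in the same way in both arms and then counting. A judgement about cause is useful as additional information. Used as the entry condition, it means that an event nobody links to the study leaves no trace, and it cannot be recovered when the arms are compared.

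The events exposed to that condition here are serious ones. A non-cardiovascular death, or an admission for a reason outside the five types, belongs in the residual category. The trial has no upper age limit and deliberately reaches older patients, so such events within 12 months are plausible. The Conclusions say that the intervention will be taken towards standard primary care if it proves effective. A statement about its safety would then rest on a record whose coverage of unlisted serious events is unclear.

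**Working it through.** No arithmetic applies. The article gives no adverse-event rate, count or harms analysis to reproduce. The check is a comparison of the text.

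1. **Scope of the two sentences.** The first covers adverse events generally. The second covers five named types without condition and all others subject to suspected relatedness. If the first sentence already secured every event, the qualifier in the second would do no work. If the second governs, the first promises more than is collected. The article does not resolve this.

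2. **What falls under the condition.** Cardiovascular deaths, and admissions caused by a fall, injury, musculoskeletal problem, hypoglycaemic episode or major cardiovascular event, fall within the named types. Deaths from other causes and admissions for other reasons do not.

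3. **Who applies the filter.** The section does not name the person who judges relatedness. Since GPs carry out all assessments, it is probably the GP, but this is an inference.

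4. **Effect if GP blinding holds.** A judgement made without knowledge of the arm should lose events to a similar degree in both arms. The result is under-counting, not a systematic shift between arms.

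5. **Effect if GP blinding fails.** Patients know their allocation and see the GP repeatedly, and the Discussion accepts that allocation may emerge in those conversations. A GP who knows that a patient receives messages and phone counselling may be readier, or less ready, to call an event related. Recording could then differ by arm. The Discussion says that loss of GP blinding will not affect outcome assessment, but a relatedness judgement is open to that influence in a way that an accelerometer step count is not.

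6. **Other routes of capture.** The article describes no other route for unlisted serious events during the 12 months. Patients consent to later access to their GP records, but the stated purpose is long-term health outcomes.

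**The case against.** The strongest reply is that the first sentence already requires adverse events to be recorded throughout, and that the second only lists what is actively asked about at visits. That reading is possible. It is why the finding is an unresolved difference in scope and not a demonstrated gap. It does not remove the need to reconcile the sentences, because a GP following the second could properly leave an unlisted death or admission off the form.

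It can also be said that targeted collection of foreseeable harms plus a residual category suits a low-risk behavioural trial, and that a condensed article leaves definitions of serious events and reporting procedures to the full protocol. Both points have weight. The absence of such detail is not held against the article here; the point concerns the collection rule that it does state.

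Three stronger readings are tempting, and the documents do not support them:

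- *A reader might infer that blinded GPs cannot make the judgement, so the counts by arm are unsound.* Blinding protects the comparison. Moreover, the condition refers to the study's implementation, which includes the advice, step goal and tracker given in both arms: "As both control and intervention arms receive from their GPs the same treatment". A blinded GP can judge relation to those. What a blinded GP cannot judge is relation to the messages and phone counselling specifically.
- *A reader might infer that all harm counts depend on attribution.* The five named types do not, and they cover the foreseeable harms of a walking programme.
- *A reader might take the Data management section as confirming that deaths go unrecorded.* That section speaks of trial outcomes, as a reason for having no monitoring committee. It says nothing about whether deaths are recorded as events.

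**Conclusion.** The point holds in limited form. The Adverse events section states an unrestricted rule and then a restricted one, and under the restricted one some non-cardiovascular deaths and unlisted unplanned admissions may go unrecorded in both arms. With GP blinding intact, the consequence is incomplete capture. Differential recording is a further risk only where blinding breaks down, which the article says cannot be excluded.

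The size cannot be stated, because the documents give neither the frequency of unlisted serious events nor the share that would be thought related. The conclusion assumes that the second sentence guides what is entered at the assessments and, for the risk of differential recording, that the GP makes the judgement. The primary outcome and the five named event types are untouched. This is a modest weakness that is cheap to correct.

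**What to change.** Reconcile the two sentences so that one rule applies:

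- Record every death and every unplanned hospital admission in both arms at the existing 3-, 6- and 12-month assessments, whatever the suspected relation to the study.
- Keep the five named event types as they are.
- Enter relatedness in a separate field after the event is recorded, not as a condition for recording it.
- Tabulate deaths and unplanned admissions by arm.

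The cost is slightly more form entry: with 340 patients and three assessments each, at most 340 × 3 = 1,020 additional item entries across 21 practices, presumably mostly negative. GPs already follow these patients and hold their records, so no extra visit, staff or procedure is needed.
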